#### *Conduct consent*

We use the deferred consent concept for participation. In this cluster randomized trial, the compared groups both consist of standard care (i.e. NVK guideline or EOS calculator, see chapter 3 and 6.2). Consent for standard care is not required. Consent for data collection of standard care and completing a questionnaire will be gained by the investigator/research nurse. Most of the time this will be within the first 24 hours after birth. We may gain consent in a later phase (more than 24 hours after birth), since we think it is reasonable and achievable to gain consent during normal working hours. No data will be collected from patients who refuse to participate.

There are two consent forms: one for permission to use data of the child, which has to be signed by both parents or guardians, and one for permission to use data of the mother, which has to be signed by the mother only. The consent forms consist of two pages. The first page contains general statements and specific statements about participating in the

study. On this page parents or guardians will be asked to give consent to collect data from the electronic medical records of mother and child (see chapter 3 and the patient information form), and to fill in one questionnaire about quality of life on day 14. Signing the form by (both) parent(s)/guardian(s) automatically means that they agree with these statements. There are three optional statements included on the first page, where they can choose whether they give permission. Parent(s)/Guardian(s) will be asked whether they give permission to save personal data from mother and child for a longer period to use these for future research, and to possible study-related follow-up (questionnaires) in the future (after day 14).

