In order to meet requirements of the European Regulations for Medical Devices, the EOS calculator has been developed as a smartphone application specifically for this study, and CE marking has successfully been obtained (see chapter 5). Only in the five hospitals randomized for the EOS calculator this application will be available for all physicians who have a treatment relationship with newborns at risk for EOS.

**Equality:** We use the same strategy to include and observe participating newborns to ensure that the control group and the intervention group are equally recruited and monitored. Each newborn in participating hospitals is evaluated for elevated EOS risk. In case one or more criteria for elevated maternal EOS risk or neonatal clinical signs of EOS are met (in accordance with the NVK guideline, Table 1), clinical evaluation of the newborn by a pediatric resident or pediatrician will take place within 4 hours after birth. After concluding eligibility, the advice of either the NVK guideline or the EOS calculator (depending on randomization) to observe or to start antibiotic therapy is followed. We maintain an observation period of at least 12-24 hours for the NVK guideline-group and at least 24 hours for the EOS calculator-group. These observation periods are in accordance with the advice of both guidelines. Observation in both groups will consist of controls of vital parameters (heart rate, respiratory rate, and temperature) every 3 hours by the nurse, and a minimum of two physical examinations (within 4 hours after birth and before discharge) by the physician.

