## 4. STUDY POPULATION

### 4.1 Population (base)

Newborns are eligible for participation if they have a postmenstrual age of 34 weeks or more, are 0-24 hours old, and in case at least one EOS risk factor or clinical sign of infection (suspected of EOS) is present within the first 24 hours of life.

Ten centers will include patients (five randomized to NVK guideline, five to EOS calculator use). Each center is supposed to include around 183 patients. Per center there are between 1500 and 2500 live births a year. The number of eligible patients is estimated to be between 300/year (center with 1500 live births/year and 20% suspected EOS) and 500/year (2500 live births/year and 20% suspected EOS). With an average number of patients of 2000 per center, a baseline suspected EOS of 20%, and at least 50% participation rate of eligible patients, the average number of patients per center that can participate in a one-year period is:  $2000 \times 0.2 \times 0.5 \times 1 = 200$  patients. This is more than enough for the needed 183 per center during an 18-month inclusion period. In the Netherlands there are currently no competing trials in this patient population.

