### 4.4 Sample size calculation

Superiority: In the control group we expect 40% antibiotic therapy in newborns at risk for EOS. To reduce this to 25% (reduction 15%) by use of the EOS calculator, (80% power, ICC 0,0025, alpha 0,05, 10 hospitals) a total sample size of 330 is required.

Non-inferiority: In the control group and the intervention group, we expect that 10% of newborn infants will fulfill one of the predefined safety criteria. The non-inferiority margin

is set at 15% (absolute difference 5%). The required sample size is 1640 (per cluster 164) (80% power, ICC 0,0025, alpha 0,025, 10 hospitals). Because both hypotheses regarding superiority (reduction in antibiotic therapy) and non-inferiority (adverse clinical outcome) have to be met, the study sample size equals the largest of the two sample sizes.

The potential drop-out or withdrawal is estimated at 10%. We will include 2x 915 newborn infants (total=1830), which means 183 per cluster. The analyses will be performed both according to the intention-to-treat (ITT) principle and according to a per-protocol (PP) analysis. All participants taking part in the study will be analyzed according to the ITT principle. Protocol deviations will be recorded and participants in whom major protocol deviations have occurred will be excluded from the PP analysis. These analyses will be both performed, since attending physicians are able to opt for clinical management not according to the advice of the assigned study protocol. This will be registered as a protocol violation in the eCRF, with accompanying justification (see chapter 3).

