#### *Recruitment of patients*

Within the first 24 hours after birth parents or guardians of eligible newborns (whom are at risk for EOS) will be approached by local principal investigators or research nurses, which are well trained (according to ICH GCP) and highly engaged in the study. The parent(s)/guardian(s) will receive more extensive information (in Dutch or English) in the patient information and consent form. Prior to entering the study, the investigator will explain to the parent(s)/guardian(s) the nature of the study, its purpose, procedures, expected duration, and the benefits and risks involved in study participation.

The patient will be given sufficient time to read the patient information and the informed consent form and has the opportunity to ask questions before signing the informed consent form. The investigator or research nurse will answer all study-related questions. The right to withdraw from the study at any time without prejudice will be clearly communicated. After this explanation and before any study-specific procedures have been performed, the patient, as well as the investigator/research nurse, will voluntarily sign and date an informed consent form.

The policy (observation and/or antibiotic therapy) is not conducted by participating in the study, since the assigned protocol is considered standard care for newborns with suspected EOS during the study period. (See also chapter 3 and 6.2.) No additional painful procedures will be performed. These things will make it more likely parents/guardians will give permission to participate.

A newborn is at risk for EOS if at least one maternal risk factor or neonatal clinical sign is present (in accordance with the NVK guideline, listed in table 1). After determining eligibility, the advice of either the NVK guideline or the EOS calculator is followed (depending on randomization). The observation period will be at least 12 hours for the control group (NVK guideline) and 24 hours for the intervention group (EOS calculator), which consists of routine controls of vital parameters (heart rate, respiratory rate, and temperature) every 3 hours by the nurse, and a minimum of two physical examinations (within 4 hours after birth and before discharge) by the physician.

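### Deferred consent after hospital randomisation lets enrolment depend on antibiotic start, possibly more in one arm than the other, and the plan collects too little to check its claim of equal recruitment

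*Protocol*

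**What the plan says.** Sections 3 and 6.2 of the protocol make the allocated policy the hospital's standard care for all at-risk newborns, regardless of participation, and state that hospitals and physicians are not blinded. Under section 9.2, local investigators or research nurses approach parents. Consent is deferred and is expected mostly within 24 hours of birth, but with an exception that suits working hours: "We may gain consent in a later phase (more than 24 hours after birth". The form for the child's data needs the signatures of both parents. For those who decline: "No data will be collected from patients who refuse to participate". Section 4.1 plans on "at least 50% participation rate of eligible patients". Section 4.4 defines intention-to-treat over participants only.

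On time in hospital, section 9.2 says: "The observation period will be at least 12 hours for the control group (NVK guideline) and 24 hours for the intervention group (EOS calculator". For controls, section 3 gives 12-24 hours as the minimum. Section 6.3 gives the same range for all newborns without antibiotics. For treated newborns, section 6.3 gives a minimum stay of 24-36 hours and section 9.4 gives 48 hours.

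Section 3 presents its common inclusion and observation strategy as a safeguard, meant "to ensure that the control group and the intervention group are equally recruited and monitored". The co-primary superiority outcome is antibiotic start in the first 24 hours (section 6.1.1).

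**The concern.** Enrolment happens after randomisation and often after the antibiotic decision, so the co-primary outcome may already be known when parents are asked. If treated and untreated newborns are enrolled at different rates, the enrolled antibiotic proportion is no longer the proportion among eligible newborns. If that gap differs between arms, the comparison itself is biased.

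The protocol contains a route to such a difference. Untreated newborns have a shorter minimum observation in control hospitals than in calculator hospitals, and treated newborns generally stay longer than either. A team that seeks two parental signatures in working hours may have least time with untreated controls. They would then be under-represented, the control antibiotic proportion would rise, and the reduction would look larger than it is.

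Randomising hospitals does not protect against selection that follows randomisation. The mixed model in section 8.1 sees only enrolled newborns and cannot correct it. Each hospital closes at 183 participants (section 3), so uneven capture would not show up as a shortfall in numbers.

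**Working it through.** **The plan's own figures.** Section 4.4 states: "In the control group we expect 40% antibiotic therapy in newborns at risk for EOS", then "To reduce this to 25% (reduction 15%) by use of the EOS calculator", with "80% power, ICC 0,0025, alpha 0,05, 10 hospitals) a total sample size of 330 is required".

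- Two proportions, 0.40 vs 0.25, two-sided 0.05, 80% power, pooled variance under the null: 152 per arm.
- With 5 hospitals per arm and design effect 1 + (m − 1) × 0.0025: m = 152 × 0.9975 / (5 − 152 × 0.0025) = 32.8, so 33 per hospital and 330 in total. This reproduces.
- Recruitment yield (section 4.1): 2000 × 0.2 × 0.5 = 200 per centre-year. This reproduces.

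The arithmetic is therefore sound. It takes for granted that enrolment does not depend on treatment.

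**Effect of selective enrolment.** Let p be the true antibiotic proportion among eligible newborns, c1 the share of treated newborns enrolled and c0 the share of untreated newborns enrolled. Then

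enrolled proportion = p·c1 / [p·c1 + (1 − p)·c0].

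The documents give no c1 or c0, so all values below are assumptions. With no true effect (p = 0.40 in both arms):

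| Scenario | Control c1 / c0 | Calculator c1 / c0 | Enrolled proportions | Spurious reduction |
|---|---|---|---|---|
| A | 60% / 47% | 60% / 50% | 0.240/0.522 = 46.0% vs 0.240/0.540 = 44.4% | about 1.5 points |
| B | 60% / 43% | 60% / 55% | 0.240/0.498 = 48.2% vs 0.240/0.570 = 42.1% | about 6 points |
| C | 62.5% / 41.7% (ratio 1.5) | equal | 50.0% vs 40.0% | 10 points |
| D | ratio 0.8 | equal | 0.32/0.92 = 34.8% vs 40.0% | −5.2 points (reversed) |
| E | same ratio in both arms | same | equal | 0 |

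**With a true effect.**

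- True 40% vs 25%, scenario C: 50.0% vs 25.0%, so 15 points appear as 25.
- True 40% vs 25%, scenario D: 34.8% vs 25.0%, so 15 points appear as 9.8.
- True 40% vs 25%, ratio 1.5 in both arms: 50.0% vs 33.3%, so 15 points appear as 16.7.
- True 40% vs 30%, scenario B: 48.2% vs 0.180/0.565 = 31.9%, so 10 points appear as 16.3.

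**Chance of a significant difference with no true effect.** Take 164 per hospital, design effect 1 + 163 × 0.0025 = 1.4075, and selection in controls only. At a ratio of 1.25 (about 57% vs 45% enrolled) the control proportion is 0.50/1.10 = 45.5%. The standard error is √[(0.240 + 0.248) × 1.4075 / 820] = 0.029, so z = 0.0545 / 0.029 = 1.88. The chance of significance is about 47% by the normal approximation and 38% with t on 8 degrees of freedom. At a ratio of 1.1 the figures are about 13% and 11%; at 1.5 they are about 93% and 85%.

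**Against the decision rule.** Section 8.1 also asks for at least a 15-point absolute reduction. To reach 15 points from no effect, selection in controls alone would need a ratio of (0.55/0.45) / (0.40/0.60) = 1.83. To lift a true 10 points to 15, it needs (0.45/0.55) / (0.40/0.60) = 1.23.

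**The case against.** A fair defence has several parts.

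- **The 12 versus 24 hour contrast is the widest reading.** Sections 3 and 6.3 give 12-24 hours, and section 6.3 schedules vital signs through 24 hours for untreated newborns without separating the arms. Twelve hours is a minimum, not a discharge time. This stands. It weakens the contrast but does not remove it, since section 3 still sets 12-24 hours against at least 24.
- **Early-discharged controls need not be lost.** Most consent is expected within 24 hours, and nothing ends it at discharge. This also stands: loss is a risk, not a documented fact. But consent after discharge is not provided for either.
- **Direction is not shown.** More refusals among parents of treated newborns would push the other way, and equal selection in both arms matters little. This stands.
- **Some checking is possible.** Risk factors are recorded for all participants, so the arms can be compared on their Table 1 profile, and both arms use the same eligibility criteria. That is a partial check. It limits identification bias but says little about consent that follows the antibiotic decision. The calculator emails (sections 5.1 and 10.1) exist only in intervention hospitals and cannot be traced to newborns.
- **A screening log may exist.** Figure 1 and the monitoring plan are not visible, so its absence cannot be asserted.

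A reader might also infer that the plan expects only half of families to take part. Section 4.1 gives 50% as a floor in a feasibility estimate, not as an expected rate. Nor does the document say that research nurses are unblinded. It names hospitals and physicians; for nurses this is a reasonable inference.

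**Conclusion.** The concern holds as a risk that the described data cannot adequately resolve. Consent follows randomisation, can follow the outcome, may miss up to half of eligible newborns, and leaves no data on those who refuse. The minimum time available to approach families differs by arm and by treatment. The statement of equal recruitment in section 3 therefore lacks a sufficient check.

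The documented mechanism points towards inflating the antibiotic reduction, but its net direction and size are unknown. The range of about 1.5 to 10 points, with a possible reversal, rests entirely on assumed capture rates and on a selection gap that differs between arms.

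A reader might infer that the trial is biased in favour of the calculator, or that 6 points measures that bias. The documents support neither. Nor would a spurious 6 or 10 points on its own be expected to meet the 15-point requirement in section 8.1. The more realistic danger is that a smaller true reduction is carried past that threshold.

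The conflicting statements on the control observation period (sections 3, 6.3 and 9.2) and on the stay of treated newborns (sections 6.3 and 9.4) bear on the mechanism and must be reconciled. Which of them is right is not a statistical question.

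**What to change.** In section 9.2, under the conduct of consent:

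1. Keep individual consent for participant-level data and the questionnaire.
2. Add anonymous hospital-level counts, collected identically in both arms: all eligible newborns, those approached, those consenting, and antibiotic start within 24 hours (yes/no).
3. Compare antibiotic start among all eligible newborns by arm at cluster level, as a prespecified sensitivity analysis beside the primary analysis. The details can sit in the statistical analysis plan, but the counts must be collected prospectively.
4. State one consent window for both arms that explicitly allows remote consent after discharge, up to day 14.

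Do not ask for counts of the safety composite in non-participants. It includes respiratory support through the first week and referral to intensive care, so counting it would mean following families who have not consented.

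The cost is a small ethics amendment and a routine tally at each hospital. Sample size and clinical care are untouched.

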### 9.3 Objection by minors or incapacitated subjects

The study will be conducted according to the “Code of conduct relating to expressions of objection by minors participating in medical research” approved by the Board of the Dutch Association of Paediatric Medicine (NVK) on 21 May 2001, see Appendix I. Parents or guardians are free to decide to withdraw from the study at any stage, and for any reason, without prejudicing their child’s further treatment.

### 9.4 Benefits and risks assessment, group relatedness

This study will have negligible risks and minimal burden.

**Burden:** -Newborns with antibiotic therapy: A intravenous cannula will be inserted for antibiotic treatment. According to current Dutch guidelines two blood samples will be taken: directly after birth during insertion of the intravenous cannula (blood culture; at least 1 mL, blood cell count, CRP, procalcitonin), and 24 hours after birth by vena puncture (CRP, procalcitonin). This is part of standard medical treatment. Hospital stay will be at least 48 hours, could be extended depending on the clinical condition and blood culture results (ranging from 36 hours to 10 days). - Newborns without antibiotic therapy: No blood samples taken. Clinical observation for at least 12-24 hours. This is part of standard medical treatment. - All newborns: Physical examinations will be performed at least twice (at birth and before discharge), and more often if necessary (depending on clinical findings). One questionnaire will be sent to the parents/guardians to fill in on day 14, this is extra for this study. The questionnaire includes a minimum of 22 questions, which may expand up to 32 questions (since some questions are dependent of other questions). It will take about 10-15 minutes to complete.

**Risks:** The risks associated with participation are very low because neonates will be closely observed when no antibiotics will be prescribed.

**Benefits:** More specific risk analysis. Not all subjects will benefit personally from study participation. When no antibiotics will be prescribed: no separation of mother and child, no painful procedures, and a shorter hospital stay (including fewer costs).

**Group relatedness:** This study can only be performed with this specific group of patients, as it will provide age-specific and risk factor-specific data that cannot be obtained otherwise.

### 9.5 Compensation for injury

This study is exempt from the WMO insurance obligation as there are no significant risks attributable to participation in this study. This is in accordance with article 7, paragraph 6 of the WMO.

## 10. ADMINISTRATIVE ASPECTS, MONITORING AND PUBLICATION

### 10.1 Handling and storage of data and documents

Data will be handled and analysed confidentially. Data will be collected in an electronic Case Report Form (eCRF) in Castor EDC to document eligibility, safety and efficacy parameters, and parameters necessary to evaluate endpoints. Each CRF will be completed on-site by the investigator or an authorized staff member. The data is handled confidentially, and a unique patient study number will be used to link the data to the subject in compliance with *EU General Data Protection Regulation and the Dutch Act on Implementation of the General Data Protection Regulation (in Dutch: Uitvoeringswet AVG, UAVG)*. All eCRF entries must be based on source documents.

Data of the EOS calculator will be sent to the work-affiliated email address of the authorized persons who use the calculator. A copy of this email will automatically be sent to the main research nurse. Every email contains a unique token. The email contains instructions for copying the results and the token to the electronic patient files. The results of the EOS calculator are included in the eCRF; there is no direct link from the smartphone application to Castor EDC.

Data of the questionnaire will be obtained online. This will be directly linked to Castor EDC. For detailed information about the questionnaire see 6.1.2, 6.3, 8.2.1 and 9.2.

Individual subject medical information obtained as a result of this study is considered confidential and disclosure to third parties is prohibited. Such medical information may be given to the subject's physician or to other appropriate medical personnel responsible for the subject's wellbeing. Data generated as a result of this study are available for inspection on request by the participating physicians, the IEC and the regulatory health authorities, including external site audits and inspections.

All study-related documents will be stored online at <https://www.zorgevaluatienederland.nl/eos>. Investigators of the participating hospitals will get access to this environment and all documents. General information about the study is available for everyone at the above-mentioned website, without the need of a password.

Every participating hospital has an Investigator Site File, located at their own protected server. The investigators will find the newest main documents of the study at <https://www.zorgevaluatienederland.nl/eos>. It is the responsibility of the coordinating

investigators to keep these documents up to date. The investigators at the participating hospitals are responsible for keeping local agreements and related documents up to date. The Trial Master File (TMF) is located at the protected server of the sponsor, Tergooi hospital. The TMF falls under the responsibility of the principal investigator, [name].

Documents and data will be stored for 15 years. Data management will be done according to the FAIR data principles (FORCE11). Our data will be findable, accessible, interoperable and reusable. Results will be shared as scientific publications, where possible via open access channels. Where possible, data will be shared in accordance with guidelines to promote further improvements and optimisation.

